**Figure 1 F1:**
[figure not shown]
Study diagram describing the construction of the PCI, CABG and ACS (conservatively managed) populations.

### Interventions

The interventions of interest for the three target trials are shown in table 1. Guidelines recommend low dose aspirin (75 to 100 mg/d) plus either clopidogrel (75 mg/d), prasugrel (5 mg/d or 10 mg/d) or ticagrelor (90 mg twice/d) for PCI and conservatively managed patients with ACS. For PCI patients, the interventions of interest are aspirin and clopidogrel, aspirin and prasugrel and aspirin and ticagrelor. In conservatively managed patients with ACS, clopidogrel is the most commonly prescribed second antiplatelet agent (in addition to aspirin) and a large proportion of patients are prescribed aspirin only; therefore, the interventions of interest are aspirin only (75 to 100 mg/day) and aspirin and clopidogrel. There is variation in aspirin prescription for CABG patients; some surgeons choose 75 mg/day, others 150 mg/day or 300 mg/day. Surgeons may also prescribe an additional antiplatelet agent, most commonly clopidogrel. Therefore, the comparisons of interest in CABG patients are aspirin only (any dose, reflecting variations in usual care in different hospitals) and aspirin and clopidogrel (doses as for PCI). We have specified these comparisons based on preliminary feasibility counts from CPRD, which indicate that few CABG and conservatively managed patients with ACS are prescribed aspirin and prasugrel or aspirin and ticagrelor.

In the target trials, the interventions would be assigned during the hospital stay, as soon as patients are eligible for antiplatelet therapy. Our observational data set does not have information on medication given to patients at discharge, because HES does not include medications data. Therefore, the first time at which we have information on the antiplatelet regimen to which patients were assigned in hospital is when they receive their first primary care prescription/s for aspirin or DAPT, recorded in CPRD. It is reasonable to use these as a proxy for the medications that patients started in hospital, because patients’ general practitioners (GPs) are unlikely to change the prescriptions that were started in hospital.

We will classify patients according to the first prescription recorded in CPRD during the first 2 months after hospitalisation for PCI, CABG or ACS. This 2-month window is based on variability in the amount of DAPT medication provided to patients in hospital following their PCI, CABG or ACS and hence variability in the time when they first request a repeat prescription from their general practice. A preliminary investigation showed that more than 75% of eligible patients have a prescription for one or more antiplatelet agents during this time period. If a patient only has a prescription for aspirin during the 2-month window after hospital discharge, they will be assigned to an aspirin only intervention. If patients also receive a prescription for clopidogrel, prasugrel or ticagrelor, they will be assigned to aspirin/clopidogrel, aspirin/prasugrel or aspirin/ticagrelor. If there is a prescription for more than one additional antiplatelet agent in the 2-month window, we will assign the patient to an intervention based on the agent prescribed first. For example, if a patient has an aspirin prescription and a prescription for clopidogrel before a prescription for ticagrelor, the patient will be assigned to the aspirin/clopidogrel intervention. Patients with no prescriptions in CPRD for aspirin, or aspirin and clopidogrel, prasugrel or ticagrelor within the 2-month window will be excluded from the main analysis. We will conduct sensitivity analyses of all eligible patients including those with unknown DAPT regimens or a major bleed prior to first DAPT prescription, by estimating assignment to DAPT interventions for those with no prescription data using multiple imputation based on a range of assumptions.^20^

### Outcomes

The primary outcome will be any bleeding event, classified as type 2–5 by the Bleeding Academic Research Consortium (BARC) bleeding scale.^21^ For each patient, we will identify all bleeding events in HES and CPRD during follow-up. We will not be able to identify BARC type 1 bleeding events (bleeding that is not actionable and does not cause the patient to seek treatment) as type 1 assumes there is no interaction with the health system or healthcare professionals; therefore, no bleed event will be recorded in HES or CPRD. We have specified a comprehensive list of bleeding codes in CPRD and HES (see online supplementary appendix 1). These will be categorised according to anatomical site for descriptive purposes. Secondary outcomes will be: any major bleeding event (leading to hospital admission, inpatient HES); any minor bleeding event (recorded within CPRD data); all-cause mortality; cardiovascular mortality; mortality from bleeding (these will be identified from linked ONS data); MI; stroke; additional coronary intervention.

10.1136/bmjopen-2019-029388.supp1Supplementary file 1

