**Methods and analysis:**

We will use linked Clinical Practice Research Datalink (CPRD) and Hospital Episode Statistics (HES) data to assemble populations eligible for three ‘target trials’ in patient groups: percutaneous coronary intervention (PCI); coronary artery bypass grafting (CABG); conservatively managed (medication only) acute coronary syndrome (ACS). Patients ≥18 years old will be eligible if, in CPRD records, they have: ≥1 year of data before the index event; no prescription for DAPT or anticoagulants in the preceding 3 months; a prescription for aspirin or DAPT within 2 months after discharge from the index event. The primary outcome will be any bleeding event (CPRD or HES) up to 12 months after the index event. We will estimate adjusted HR for time to first bleeding event comparing: aspirin and clopidogrel (reference) versus aspirin and prasugrel or aspirin and ticagrelor after PCI; and aspirin (reference) versus aspirin and clopidogrel after CABG and ACS. We will describe rates of bleeding in patients prescribed TT (DAPT plus an anticoagulant). Potential confounders will be identified systematically using literature review, semistructured interviews with clinicians and a short survey of clinicians. We will conduct sensitivity analyses addressing the robustness of results to the study’s main limitation—that we will not be able to identify the intervention group for patients whose bleeding event occurs before a DAPT prescription in CPRD.

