Assignment to interventions	Participants are assigned to DAPT interventions in hospital.	Participants enter the study at index procedure date for PCI and CABG, and episode start date for ACS, and will be assigned to DAPT interventions using first prescription in CPRD (within 2 months of hospitalisation) as a proxy for what they were prescribed in hospital (there are no medications data in HES). This assignment will exclude a proportion of eligible patients (those who died or experienced a major bleed that caused them to stop DAPT, or patients who have no prescription for DAPT within the 2-month window); we will identify and describe the characteristics of these excluded patients. In sensitivity analyses, we will address the robustness of results to different assumptions about the intervention group in those patients where the DAPT medication is unknown or a major bleed occurs prior to the first DAPT medication, by using multiple imputation models for handling missing data. Prior known information regarding the likely prescription based on patient characteristics or general policies will be incorporated in these analyses.
Follow-up	Starts at assignment to intervention and ends at first bleed or 12 months from assignment (whichever comes first).	Starts at time of hospitalisation for PCI, CABG or ACS and ends at first bleed or 12 months from hospitalisation (whichever comes first).
Primary outcome	Any bleed within 12 months of the start of DAPT (DAPT is prescribed at hospitalisation for PCI, CABG or ACS).	Any bleed within 12 months of hospitalisation for PCI, CABG or ACS.
Analysis	Intention to treat	According to first prescription for DAPT in CPRD

CABG, coronary artery bypass grafting; CRPD, Clinical Practice Research Datalink; DAPT, dual antiplatelet therapy; HES, Hospital Episode Statistics; PCI, percutaneous coronary intervention; PICO, Population, intervention, comparator, outcome.

In patients who have undergone PCI, estimate the effect on bleeding events of assignment to aspirin and clopidogrel (reference) versus aspirin and prasugrel or aspirin and ticagrelor.In patients who have undergone CABG, estimate the effect on bleeding events of assignment to aspirin (reference) versus aspirin and clopidogrel.In patients who are conservatively managed after presenting with ACS, estimate the effect on bleeding events of assignment to aspirin (reference) versus aspirin and clopidogrel.

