### Study populations

Eligibility and exclusion criteria for the three target trials (for patients undergoing PCI, patients undergoing CABG or patients hospitalised and conservatively managed for ACS) are listed in table 1. We will identify eligible patients who are included in Clinical Practice Research Datalink (CPRD) and eligible for linkage with Hospital Episode Statistics (HES) and Office for National Statistics (ONS) mortality data (because they have a valid NHS number and are registered at a practice that was participating in the linkage programme). Patients are included if they had a PCI, CABG or ACS (index event) record in HES during the study period (1 April 2010–31 January 2017), and have at least 1 year of linked CPRD-HES data before the date of their index event. They must also have been prescribed one of the treatment regimens being compared in the target trial corresponding to their index event. One year’s data preceding eligibility for the target trial is adequate to apply most of the exclusion criteria and determine comorbidities and medication history: such information would be collected at baseline in a randomised trial. The following Office of Population Censuses and Surveys (OPCS) procedure codes (PCI and CABG) and International Classification of Diseases (ICD-10) codes (ACS no procedure) will be used to identify patients: PCI, K49, K50 & K75; CABG, K40, K41, K42, K43, K44, K45 & K46; ACS without a procedure, I20.0, I21, I22, I24.9 (with no OPCS code for PCI or CABG in the same hospital admission). Figure 1 shows full details of the inclusion and exclusion criteria.

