### Statistical analyses

We will describe temporal changes in DAPT prescribing and bleeding for PCI, CABG and ACS populations. We will use descriptive statistics to summarise the characteristics of the different intervention groups and standardised mean differences to compare them. We will estimate rates of bleeding (number of events/person time) with 95% CIs for each group. We will separate major and minor bleeding since adverse events of each type have different health and resource use consequences.

Analyses will estimate the effects of assigned intervention (analogous to an intention-to-treat analysis of a randomised trial) for the antiplatelet regimens corresponding to the first prescription of aspirin or DAPT in CPRD (see Interventions). We will use parametric survival models to estimate adjusted HRs with 95% CIs for the time to first bleeding event, comparing intervention groups for each target trial. Exploratory analyses, including assessment of proportional hazards assumptions, will be used to inform the choice of survival distribution (eg, Weibull). Estimated time-dependent event probabilities will be used to update existing cost-effectiveness models.^26^ The confounding factors to be included in the model (which will be identified as described previously and grouped into confounding domains from our data set), the modelling strategy and the approach to handling correlated covariates will be documented in a data analysis plan. Participants free from a bleeding event will be censored at 12 months after the index event. For secondary endpoints, we will use survival models to estimate adjusted HRs with 95% CIs for time to first event. For mortality outcomes, we will take account of the competing risks of death due to other causes.

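### The primary outcome counts any bleed but draws only on CPRD and HES, so a fatal bleed recorded only on the linked ONS death record is analysed as bleed-free

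*Protocol article*

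**What the plan says.** The Outcomes section defines the primary outcome broadly: "The primary outcome will be any bleeding event, classified as type 2–5 by the Bleeding Academic Research Consortium (BARC) bleeding scale". It then names the sources, "For each patient, we will identify all bleeding events in HES and CPRD during follow-up", and the abstract agrees: "The primary outcome will be any bleeding event (CPRD or HES) up to 12 months after the index event". The code list has the same scope: "We have specified a comprehensive list of bleeding codes in CPRD and HES".

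ONS data appear in two places. Study populations makes linkage a condition of inclusion, since patients must be "eligible for linkage with Hospital Episode Statistics (HES) and Office for National Statistics (ONS) mortality data". Outcomes then lists, among the secondary outcomes, "mortality from bleeding (these will be identified from linked ONS data". Nothing in the article adds those deaths to the primary outcome.

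The other secondary bleeding outcomes are also tied to a source. A major bleed is one that leads to a hospital admission (inpatient HES), and a minor bleed is one recorded in CPRD.

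Statistical analyses states that "Participants free from a bleeding event will be censored at 12 months after the index event". It mentions competing risks only for the mortality outcomes.

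**The concern.** A primary outcome called any bleeding event should contain every fatal bleed that the study itself recognises. Here it need not. A patient who dies of a bleed outside hospital, with no earlier HES or CPRD bleeding entry, is an event for bleeding mortality and a non-event for the primary. That patient is also neither a major bleed (no admission) nor a minor one (no CPRD record).

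Three things are at stake:

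- **Coherence.** The results could show bleeding deaths among patients reported as having had no bleed.
- **Selective loss.** Only fatal bleeds are affected, so the most severe events are the ones that go missing.
- **Use of the estimates.** The time-dependent event probabilities are meant to update cost-effectiveness models, and the Introduction stresses uncertainty in the absolute risk of bleeding. These deaths would be absent from the primary, major and minor rates alike.

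The article does consider what its sources cannot see, but names only BARC type 1 events, because those patients have no contact with the health system. A fatal bleed with no recorded contact is missed for the same reason. Unlike type 1 events, it can be recovered from data the study already holds.

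**Working it through.** **1. One patient under each rule.** Take a patient with a qualifying prescription who later dies of a bleed recorded only by ONS.

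| Outcome | Stated source | Status |
|---|---|---|
| Primary, any bleed | CPRD or HES | No event |
| Major bleed | Inpatient HES | No event |
| Minor bleed | CPRD | No event |
| Death from bleeding | ONS | Event |

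Table 1 does not list death as an end of follow-up. Read literally, the censoring rule therefore keeps this patient at risk to 12 months, past the date of death.

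**2. The plan's own figures.** Inputs from Sample size are bleeding rates of 5% (aspirin), 9% (aspirin/clopidogrel) and 12% (aspirin with prasugrel or ticagrelor), and the feasibility counts.

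- ACS: 8148 × 0.05 + 3082 × 0.09 = 684.8 (stated 680)
- CABG: 2556 × 0.05 + 595 × 0.09 = 181.4 (stated 180)
- PCI: 6738 × 0.09 + 842 × 0.12 = 707.5 for prasugrel; 6738 × 0.09 + 770 × 0.12 = 698.8 for ticagrelor (stated 700)

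Detectable HR = exp[(z₀.₉₇₅ + z_power) / √(D·p(1−p)(1−R²))], with p = 1/(1 + ratio) and a two-sided 5% level assumed. For ACS, D = 680, p = 1/3.5 and R² = 0, which gives 1.317 (90% power) and 1.268 (80%), against 1.32 and 1.27 in Table 2. All 18 entries reproduce to within about 0.01.

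**3. How many events might be missed (assumed inputs).** The documents give neither a bleeding-death rate nor the share recorded only by ONS. Assume a 12-month risk of bleeding death of 0.2% to 0.5%, with 25% to 50% of those deaths recorded only by ONS. For ACS, 8148 + 3082 = 11,230 patients.

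- Low: 11,230 × 0.002 = 22 deaths; 25% is about 6; 6/680 = 0.9%
- High: 11,230 × 0.005 = 56 deaths; 50% is about 28; 28/680 = 4.1%

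**4. Effect on power.** Suppose 0.5% to 5% of planned events are missed, and take power at the stated 90% HR with R² = 0.

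| Cohort | Events left | Power |
|---|---|---|
| PCI (HR 1.48) | 697 to 665 | 0.902 to 0.888 |
| CABG (HR 1.83) | 179 to 171 | 0.899 to 0.885 |
| ACS (HR 1.32) | 677 to 646 | 0.904 to 0.890 |

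**5. Effect on the HR (assumed inputs).** HR = ln(1 − p₁)/ln(1 − p₀). With the planning rates this is 1.839 for 5% v 9% and 1.355 for 9% v 12%. Adding an ONS-only risk to each group gives:

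| ONS-only risk, reference / comparator | 5% v 9% | 9% v 12% |
|---|---|---|
| 0.1% / 0.1% | 1.823 | 1.352 |
| 0.1% / 0.2% | 1.844 | 1.364 |
| 0.1% / 0.3% | 1.865 | 1.376 |
| 0.2% / 0.2% | 1.807 | 1.348 |
| 0.2% / 0.4% | 1.849 | 1.372 |
| 0.5% / 0.5% | 1.765 | 1.338 |
| 0.5% / 1.0% | 1.862 | 1.395 |

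The inputs in step 3 imply an ONS-only risk of 0.05% (0.2% × 25%) to 0.25% (0.5% × 50%), so the 0.5% rows are a stress test. The HR with ONS deaths added lies on both sides of the starting value.

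**The case against.** The strongest reply is that this is a small matter of wording. Its size is wholly assumed, and even generous inputs barely move power or the HR. Fatal bleeds are not lost to the study, because bleeding mortality is a pre-specified outcome analysed with competing risks, so a reader would see an excess by regimen. Patients with no qualifying prescription within 2 months, including those who die before one, are outside the main analysis and go to the multiple-imputation sensitivity analysis. The protocol also expects most bleeds to come early. All of this stands and limits the size of the problem. It does not remove it: patients who die of a bleed after a first prescription are still misclassified, and the imputation addresses unknown treatment, not a missed outcome.

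A reader might infer four stronger things that the documents do not support:

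- **That the rule biases the comparison in favour of the more potent regimens.** No regimen-specific data on ONS-only deaths are given, and step 5 shows shifts in both directions.
- **That the cost-effectiveness model loses its costliest events.** There are no cost figures, and a death without admission may use few resources.
- **That the two outcomes contradict each other.** They have different declared sources. They fail to nest, but neither statement is false.
- **That the definition of major bleeding is wrong.** It rests on admission by design, because major and minor bleeds differ in resource use.

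The article does not describe BARC types 2 to 5, so the point rests on the words any bleeding event and on the study's own recognition of bleeding deaths.

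**Conclusion.** The point holds as a flaw in the stated ascertainment rule. It is not a detail left to the analysis plan, because the article names the primary outcome's sources twice and assigns ONS elsewhere. As written, an ONS-only bleeding death in the main analysis is a bleeding death and, in the primary analysis, bleed-free.

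The effect is probably small: about 1% to 4% of ACS primary events, if bleeding deaths run at 0.2% to 0.5% and 25% to 50% of them are recorded only by ONS. Neither figure is in the documents, and the range ignores the exclusion of deaths before a first prescription. Power at the stated HRs stays near 0.89 to 0.90. In the scenarios run, the HR moves from 1.84 to between 1.77 and 1.87, or from 1.36 to between 1.34 and 1.40 for PCI, with no direction that can be known in advance. The case for change rests on a coherent outcome and complete absolute event rates, not on power or a demonstrated bias.

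**What to change.** Define the primary outcome as the first bleed in CPRD, HES or ONS. Count a death that meets the study's existing bleeding-mortality definition as a primary event on the date of death when no earlier bleed is recorded. Using that definition avoids a second, competing rule for what makes a death a bleeding death. Make the same change in the abstract, Outcomes and Table 1.

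Keep the admission-based definition of major bleeding. Report ONS-only fatal bleeds as a separate category, so that the major, minor and fatal components together account for the primary outcome and can be passed to the economic model.

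The cost is small: revised wording, one extra code match, and a primary outcome that draws on a third data source. The ONS linkage is already in place, and these deaths must be identified anyway for the secondary outcome.

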## Introduction

Dual antiplatelet therapy (DAPT), a combination of aspirin and either clopidogrel, prasugrel or ticagrelor, is recommended for secondary prevention of ischaemic events (heart attack and stroke) in people with coronary artery disease. Guidelines recommend that patients are treated with DAPT for 6 to 12 months following myocardial infarction (MI) and coronary interventions (percutaneous coronary intervention [PCI] and coronary artery bypass grafting [CABG])^1–3^ and support the use of the more potent antiplatelet inhibitors ticagrelor and prasugrel.^2^ Antiplatelet agents reduce the risk of ischaemic events, by preventing the formation of clots in atherosclerotic coronary arteries and within stents (following PCI) or grafts (following CABG), but increase the risk of bleeding.^4^ Randomised controlled trials (RCTs) have shown that adding clopidogrel to aspirin leads to 1% excess risk of major bleeding (requiring admission to hospital) compared with aspirin alone.^5 6^ Prasugrel and ticagrelor reduce the risk of ischaemic events further but also further increase the risk of bleeding.^7^ Some patients (eg, those with existing atrial fibrillation or those who develop atrial fibrillation after PCI, CABG or acute coronary syndrome [ACS]) are prescribed an anticoagulant (eg, warfarin, dabigatran, rivaroxaban, apixaban) in addition to DAPT (triple therapy [TT]), which further increases the risk of bleeding.

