‘Real world’ bleeding events that do not require any intervention are likely to be much more frequent than those reported in RCTs, which excluded patients at high risk of bleeding and mainly reported only on major bleeding. Bleeding events that do not result in hospitalisation are largely managed in primary care and may have a significant clinical and economic impact.^8^ Minor and nuisance bleeding (nose and gum bleeds, bruising and prolonged bleeding from cuts) may also reduce adherence to DAPT^9^ and non-adherent patients may be at increased risk of a secondary ischaemic episode.^10^ Only three studies have reported the incidence and consequences of nuisance bleeding after DAPT^11–13^; these suggest that nuisance bleeding is common (affecting 29%–38% of patients) and impacts on adherence (11% of patients in one study discontinued clopidogrel^12^). A nested case–control study using the Health Improvement Network (a UK primary care database) reported an increased risk of upper gastrointestinal bleeding with clopidogrel and aspirin compared with aspirin alone (relative risk, 2.08; 95% CI 1.34 to 3.21).^14^

The economic impact of bleeding events associated with DAPT is also poorly characterised, in particular for minor bleeding events and their impact on health-related quality of life.^8^ This is not surprising given that health economic analyses often lack detailed data on adverse effects of interventions, despite consensus that such effects should be considered.^15 16^ To ensure appropriate decisions are made about which DAPT regimens to use in clinical practice, the health and resource use consequences of minor and major bleeding events should be incorporated into assessments of cost-effectiveness. For DAPT, this entails accounting for uncertainty in the absolute risk of bleeding, the impact of different bleeding events on health-related quality of life and treatment adherence and subsequent risk of secondary ischaemic events and the cost implications of managing these bleeding events.

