### Follow-up

The start of follow-up (the index event) will be the date of the index hospital procedure (PCI, CABG) or start date of the hospital episode that contains the ACS diagnosis (ACS). Patients will be followed up until 12 months after the index event, since DAPT is prescribed for 12 months in accordance to guidelines.

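### Minor bleeding is defined as any bleed in CPRD, without excluding bleeds that led to an admission, so the major and minor secondary outcomes overlap

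*Protocol article*

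**What the plan says.** The primary outcome is any bleed of BARC type 2 to 5, and both databases are searched for every patient: "For each patient, we will identify all bleeding events in HES and CPRD during follow-up". Among the secondary outcomes, the Outcomes section lists "any major bleeding event (leading to hospital admission, inpatient HES") and "any minor bleeding event (recorded within CPRD data"). The BARC scale defines the primary outcome only; it is not used to divide major from minor.

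Statistical analyses gives the reason for the division: "We will separate major and minor bleeding since adverse events of each type have different health and resource use consequences". It also plans survival models for time to first event for the secondary endpoints, and says that estimated event probabilities will update cost-effectiveness models.

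Two statements in the Introduction show what the terms are meant to cover. Major bleeding is glossed as bleeding that needs admission ("1% excess risk of major bleeding (requiring admission to hospital) compared with aspirin alone"), and "Bleeding events that do not result in hospitalisation are largely managed in primary care".

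Under Follow-up, time at risk begins in hospital: "The start of follow-up (the index event) will be the date of the index hospital procedure (PCI, CABG"), or at the start of the episode containing the diagnosis for ACS.

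**The concern.** The condition that makes a bleed minor in the Introduction, that it did not result in hospitalisation, is missing from the definition in Outcomes. What remains is a source label. If the practice codes an admitted bleed, for example from a discharge letter, the CPRD record meets the minor definition while the HES record meets the major one.

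Three results are exposed:

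- **Rates by type.** Minor-bleed rates contain some major bleeds.
- **The minor-bleed HR.** Each arm's minor rate gains a fraction of its major rate, so the comparison of minor bleeding borrows from the comparison of major bleeding.
- **Economic inputs.** If probabilities by type feed the cost-effectiveness models, a double-coded bleed can be costed once as an admission and again as a primary-care event.

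A related gap concerns bleeds coded during the index stay. They fall within follow-up but did not lead to that admission, and the text does not say which grade they take.

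**Working it through.** **Text check.** The plan states no figure that depends on this point, so the definitions are applied as printed to four kinds of bleed.

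1. Managed by the practice, no admission, coded in CPRD: minor only.
2. Leads to an admission, coded in inpatient HES, not coded in CPRD: major only.
3. Leads to an admission, coded in inpatient HES and also in CPRD: major and minor. No precedence or matching rule is printed.
4. Occurs in the index stay and is coded in inpatient HES. If inpatient HES coding is enough, it is major. If it must have led to an admission, it is not major, and it is minor only if the practice codes it. The text does not choose between these readings.

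Case 3 is enough to show that the two outcomes are not mutually exclusive.

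**Size of the overlap (assumed inputs).** Take the 700 expected PCI events from Sample size. Assume that a share h are hospital bleeds, that a fraction q of these are also coded in CPRD, and that every other bleed is in CPRD. Only the 700 comes from the documents.

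- Counted as both = 700 × h × q
- Minor as printed = 700 × (1 − h) + 700 × h × q
- h = 20%, q = 25%: 35 counted as both; minor as printed 560 + 35 = 595; share 35/595 = 6%
- h = 40%, q = 75%: 210 counted as both; minor as printed 420 + 210 = 630; share 210/630 = 33%

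**Effect on 12-month risk (assumed inputs).** Let true minor risk be m = 6% and major risk M = 3%. Apparent minor risk = m + qM.

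- q = 0.3: 6% + 0.9% = 6.9%, which is 15% too high
- q = 0.7: 6% + 2.1% = 8.1%, which is 35% too high

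These are upper bounds on those inputs. A patient with both a major and a true minor bleed already has a minor event, so the duplicate adds nothing to first-event incidence.

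**Effect on the ratio between arms.** If q is the same in both arms, the apparent minor risk ratio is a weighted mean, (1 − w) × minor ratio + w × major ratio, where w = qM/(m + qM) in the reference arm. Within-patient overlap is again ignored, and the risk ratio stands in for the HR.

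- Minor ratio 1.0, major ratio 1.5 (3% v 4.5%), q = 0.3: 7.35/6.9 = 1.07
- Same ratios, q = 0.7: 9.15/8.1 = 1.13
- Minor ratio 1.3, major ratio 1.5, q = 0.5: (7.8 + 2.25)/(6 + 1.5) = 10.05/7.5 = 1.34
- Equal minor and major ratios: no change

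The direction follows from the definitions. The amount depends on inputs that the documents do not give.

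**Primary outcome.** This is time to first bleed of any type in either source. A second record of the same bleed cannot create a second first event; at most, a difference in recorded dates moves the event time.

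**The case against.** The strongest reply is that the labels are shorthand. Read with the Introduction and with the promise to separate the two types, the intention is plainly an exclusive split. Record matching is also detail that an article may leave to the code list in the supplementary appendix or to the data analysis plan, neither of which is shown. Part of this stands: the intention is clear, and a matching rule may exist elsewhere. But the article does more than omit a rule. It prints a definition of minor bleeding that admits hospital bleeds. What it assigns to the data analysis plan is confounders, modelling strategy, correlated covariates and subgroups, not outcome definitions.

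It is also fair to object that the harm is limited to secondary outcomes, that the HR moves only when the major and minor HRs differ, and that every percentage above rests on assumed inputs. All of that stands.

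A reader might go further in three ways that the documents do not support:

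- **That index-stay bleeds count as neither major nor minor.** This requires the condition of leading to an admission to be applied strictly and the practice never to code the bleed. If HES coding alone decides, they are major, and nothing says they are absent from CPRD. Table 1 and the Interventions section also expect major bleeds before the first CPRD prescription, a period that includes the index stay. The grade is unclear, not fixed as neither.
- **That both outcomes are defined purely by database.** The major definition also has a clinical condition.
- **That the CPRD date of a double-coded bleed is always later than the true date.** The documents do not say how these dates are assigned.

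**Conclusion.** The point holds for the two bleeding secondary outcomes. As printed they overlap, because an admitted bleed also coded by the practice meets both definitions, and this conflicts with the plan's stated purpose in separating them. Minor-bleed rates are biased upwards. The minor-bleed HR is biased towards the major-bleed HR where the two differ, assuming double coding is similar across arms.

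The documents do not allow the size to be computed. The illustrations give 6% to 33% of minor bleeds misclassified on one set of assumptions and an inflation of at most 15% to 35% on another. They show that the effect could matter, not what it is. The primary outcome is not materially affected, and the sample size does not depend on the split. The grade of index-stay bleeds is a smaller ambiguity that should be settled at the same time. It may also bear on who is treated as having a major bleed before the first prescription in the multiple-imputation sensitivity analyses.

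**What to change.** - Define minor bleeding as a CPRD-recorded bleed with no matching HES bleed admission within a prespecified window. The length is a judgement; 30 days either side is one possibility.
- Attribute matched CPRD records to the major event and use its HES date.
- Vary the window in a sensitivity analysis, for example 7 and 90 days, and report how many CPRD records are matched under each.
- State how bleeds coded within the index admission are graded, either within major bleeding or as a separate category, and use the same rule wherever the plan refers to a major bleed before the first prescription.
- If a matching rule already exists in the appendix or the data analysis plan, cite it in the outcome definition.

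The cost is a change of wording and a date-matching step on linked data already held. The drawback is that a genuine, separate bleed managed by the practice close to an admission may be absorbed into the major event; the varied window would show how much this matters. The condition that a major bleed leads to an admission need not be changed to remove the overlap.
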